### **10.2.2 Serious Adverse Events**

All serious adverse events occurring during clinical studies must be reported to the appropriate sponsor contact person by investigational staff within 24 hours of their knowledge of the event.

Information regarding serious adverse events will be transmitted to the sponsor using the Serious Adverse Event Form, which must be completed and signed by a member of the investigational staff, and transmitted to the sponsor within 24 hours. The initial and follow-up reports of a serious adverse event should be made by facsimile (fax).

All serious adverse events that have not resolved by the end of the study, or that have not resolved upon discontinuation of the subject’s participation in the study, must be followed until any of the following occurs:

- The event resolves
- The event stabilizes
- The event returns to baseline, if a baseline value is available
- The event can be attributed to factors other than study procedures or study conduct
- It becomes unlikely that any additional information can be obtained (subject or health care practitioner refusal to provide additional information, lost to follow-up after demonstration of due diligence with follow-up efforts)

The cause of death of a subject in a clinical study, whether or not the event is expected or associated with a study required procedure, is considered a serious adverse event. Any event requiring hospitalization (or prolongation of hospitalization) that occurs during the course of a subject’s participation in a clinical study must be reported as a serious adverse event, except hospitalizations for the following:

- Social reasons in absence of an adverse event
- Surgery or procedure planned before entry into the study (must be documented in the CRF)

### **10.2.3 Pregnancy**

Any subject who becomes pregnant must be promptly withdrawn from the study and no further study procedures should be performed.

### **10.3 Contacting Sponsor Regarding Safety**

The names (and corresponding telephone numbers) of the individuals who should be contacted regarding safety issues or questions regarding the study are listed on the Contact Information page(s), which will be provided as a separate document.

## **11 ETHICAL ASPECTS**

### **11.1 Study-Specific Design Considerations**

None of the procedures may necessarily benefit the subjects and there is the potential of adverse events in particular related to the procedures. For asthmatic subjects, it is possible that knowledge of the inflammatory phenotype of the subjects could help their physician guide future therapy.

For subjects who are undergoing sputum induction, common expected effects include salty taste, retching, vomiting coughing, dizziness and faintness. Most of these are mild and self-limited. However, depending on the severity of these symptoms, the PI may decide to record an AE. Subjects, particularly those with asthma may experience dyspnea, wheeze due to bronchospasm. Again, in most cases the symptoms are mild and self-limiting. The PI will decide as to whether such asthma symptoms require recording as an adverse event on a case-by-case basis. The overall risk of sputum induction is low and there are no reported cases of death (see Study Reference Manual for safety monitoring). If a subject has an unnoticed infectious disease (eg, active TB), there may be a risk of exposing study personnel to infection.

The bronchoscopy procedure consists of the administration of lidocaine, atropine and agents used for conscious sedation and the procedure itself. There are potential adverse events that arise from lidocaine including lidocaine toxicity which is dose related and can be prevented by recording the amounts administered and setting an upper limit (see Study Reference Manual). Atropine may result in tachycardia, worsening of glaucoma, and urinary retention. Subjects should be screened for these conditions before bronchoscopy. The medications used for conscious sedation vary from center to center but include opiates and short-acting intravenous benzodiazepines. The risks of these agents include allergic reactions, excessive sedation with respiratory depression and hypoxemia, hypercarbia and apnea. Careful titration of medications and monitoring of all subjects by skilled personnel including continuous ECG and oximetry should help avoid these complications.

The bronchoscopy procedure includes insertion of the scope via a naris or the oral cavity and hence through the vocal cords into the lower respiratory tree. While an extremely

safe procedure, complications can occur that, in some cases, may be serious and even result in death. A non-exhaustive list includes nasal pain, epistaxis, retching, vomiting and aspiration, vocal cord spasm, bleeding from the lower airways, bronchospasm, hypoxemia and pneumothorax. Death, while rare, can occur due to bleeding or asphyxia particularly in those with asthma. Careful screening of subjects and skilled operators and precautions as mandated in the Study Reference Manual will help reduce the chance that these procedures are harmful.

Potential subjects will be fully informed of the risks and requirements of the study and, during the study, subjects will be given any new information that may affect their decision to continue participation. They will be told that their consent to participate in the study is voluntary and may be withdrawn at any time with no reason given and without penalty or loss of benefits to which they would otherwise be entitled. Only subjects who are fully able to understand the risks, benefits, and potential adverse events of the study, and provide their consent voluntarily will be enrolled.

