### **10.1 Definitions**

#### **10.1.1 Adverse Event Definitions and Classifications**

##### **Adverse Event**

An adverse event is any untoward medical occurrence in a clinical study subject administered a medicinal (investigational or non-investigational) product or underwent a study procedure. An adverse event does not necessarily have a causal relationship with the treatment. An adverse event can therefore be any unfavorable and unintended sign (including an abnormal finding), symptom, or disease temporally associated with the use of a medicinal (investigational or non-investigational) product or study procedure, whether or not related to that medicinal (investigational or non-investigational) product or study procedure. (Definition per International Conference on Harmonisation [ICH]).

As no therapeutic intervention is involved with this study, only events temporally associated with a study procedure and determined to be possibly, probably or very likely related to a study procedure including spirometry, bronchoscopy, induced sputum, methacholine challenge and blood collection will be reported as adverse events.

This includes any occurrence that is new in onset or aggravated in severity or frequency from the baseline condition, or abnormal results of diagnostic procedures, including laboratory test abnormalities.

Note: The sponsor collects adverse events starting with the signing of the informed consent form (refer to Section 10.2.1, All Adverse Events, for time of last adverse event recording).

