#### **10.1.3 Severity Criteria**

An assessment of severity grade will be made using the following general categorical descriptors:

**Mild:** Awareness of symptoms that are easily tolerated causing minimal discomfort and not interfering with everyday activities.

**Moderate:** Sufficient discomfort is present to cause interference with normal activity.

**Severe:** Extreme distress causing significant impairment of functioning or incapacitation. Prevents normal everyday activities.

The investigator should use clinical judgment in assessing the intensity of events not directly experienced by the subject (eg, laboratory abnormalities).

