### **10.2 Procedures**

#### **10.2.1 All Adverse Events**

Only adverse events related to the study procedures, whether serious or non-serious, will be reported from the time a signed and dated informed consent form is obtained until completion of the last study-related procedure (may include contact for follow-up of safety). Serious adverse events, including those spontaneously reported to the investigator within 30 days after the last study procedure, must be reported using the Serious Adverse Event Form. The sponsor will evaluate any safety information that is spontaneously reported by an investigator beyond the time frame specified in the protocol.

All events related to study procedures that meet the definition of a serious adverse event will be reported as serious adverse events. Adverse events related to study procedures, regardless of seriousness or severity, must be recorded using medical terminology in the source document and the CRF. Whenever possible, diagnoses should be given when signs and symptoms are due to a common etiology (eg, cough, runny nose, sneezing, sore throat, and head congestion should be reported as “upper respiratory infection”). Investigators must record in the CRF their opinion concerning the relationship of the adverse event to study procedures. All measures required for adverse event management must be recorded in the source document and reported according to sponsor instructions.

The sponsor assumes responsibility for appropriate reporting of study procedure related adverse events to the regulatory authorities if required. The investigator (or sponsor where required) must report these events to the appropriate Independent Ethics Committee/Institutional Review Board (IEC/IRB) that approved the protocol unless otherwise required and documented by the IEC/IRB.

Subjects (or their designees, if appropriate) must be provided with a “study card” indicating the study number, the investigator’s name and a 24-hour emergency contact number.

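### Section 11.1 makes recording of adverse events after sputum induction discretionary, while Section 10.2.1 makes it mandatory at any severity; the two must be reconciled

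*Protocol*

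**What the plan says.** Section 11.1 describes the expected effects of sputum induction in two groups and gives each its own recording rule.

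- For the common effects (taste, gagging, cough, light-headedness and the like), it says that "depending on the severity of these symptoms, the PI may decide to record an AE".
- It then says "Subjects, particularly those with asthma may experience dyspnea, wheeze due to bronchospasm", remarks that these are usually mild and settle by themselves, and adds: "The PI will decide as to whether such asthma symptoms require recording as an adverse event on a case-by-case basis". No criterion for that decision is stated.

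Section 10 sets the general rule.

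- Section 10.1.1 limits reportable adverse events to "only events temporally associated with a study procedure and determined to be possibly, probably or very likely related to a study procedure". Induced sputum is one of the procedures it names. It also covers anything new, or worse than at baseline.
- Section 10.1.3 defines the Mild grade as "Awareness of symptoms that are easily tolerated causing minimal discomfort and not interfering with everyday activities".
- Section 10.2.1 states: "Adverse events related to study procedures, regardless of seriousness or severity, must be recorded using medical terminology in the source document and the CRF".

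Section 9.5 includes in the analysis, and lists, the adverse events that are reported.

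**The concern.** The protocol gives investigators two recording rules for the same event. Section 10.2.1 makes severity irrelevant to whether a related event is recorded. Section 11.1 makes severity the guide for one group of induction effects and leaves the other to an unstated judgement.

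An event that is not recorded never reaches the Section 9.5 analysis or listings. Several centers will apply the rule. Two investigators can see the same mild wheeze after the same procedure, one recording it and one not, and each can point to protocol text in support. The completeness of the procedure-related adverse event data, and its consistency from site to site, would then depend partly on local habit.

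**Working it through.** The plan states no figure on this point, so the check is a comparison of the texts, followed by a count of how often the situation can arise.

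**Test case.** An asthmatic subject with no wheeze beforehand develops a mild, brief wheeze after the baseline induction.

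1. *Is it an adverse event under Section 10.1.1?* It is new relative to baseline, it follows a named study procedure in time, and Section 11.1 itself presents wheeze as an effect of induction, so at least possible relatedness is hard to deny. The definition is met.
2. *Does mildness take it out?* No. Section 10.1.1 has no severity threshold, and Section 10.1.3 has a grade for just this kind of symptom. A Mild grade would have little purpose if mild events were not recorded.
3. *What does Section 10.2.1 require?* Recording in the source document and the CRF, because the duty applies "regardless of seriousness or severity, must be recorded". Investigator judgement enters as an opinion on relationship, and that opinion is itself entered in the CRF.
4. *What does Section 11.1 allow?* The investigator may decide that the wheeze does not need recording.
5. *Do the two agree?* No. Under Section 10 the wheeze is recorded as a Mild related event. Under Section 11.1 it may be omitted.
6. *What follows in the analysis?* If it is omitted, it is absent from the events that Section 9.5 includes and lists.

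Section 9.5 gives a useful contrast. Its own example is an asthma exacerbation after bronchoscopy: once the investigator considers it related, it should be recorded. No further choice is offered. Section 11.1 adds one for induction.

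**How often the situation can arise.** The Schedule of Events plans induction at screening, baseline and 6 months for asthmatic subjects, and at screening and baseline for healthy subjects. With the planned enrolment of about 150 and 30:

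150 × 3 + 30 × 2 = 450 + 60 = 510 scheduled inductions.

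This is before repeat attempts, inductions in subjects who then fail screening, and withdrawals. It counts procedures, not events. The recorded rate equals the true symptom rate multiplied by the probability that the investigator records the symptom. The protocol gives neither factor, so the shortfall cannot be calculated from it.

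**The case against.** The strongest defence is that Section 10.2.1 applies only once something is an adverse event, and that Section 11.1 merely leaves the threshold question to the investigator. In an asthmatic subject, whether dyspnea or wheeze exceeds the usual state does need individual judgement, and Section 9.5 also relies on the investigator's opinion of relatedness. This part stands: judgement on whether the Section 10.1.1 definition is met is proper and should remain. It does not rescue the wording. Section 11.1 already attributes the symptoms to induction, frames the decision as whether they need recording, and in the neighbouring sentence ties that decision openly to severity.

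A second defence is that Section 10 is the adverse event section, that Section 7.11 sends readers there for follow-up and capture, and that Section 11.1 is only a description of risk. That favours Section 10 as the governing text, but no sentence says so, and an investigator reading Section 11.1 would not know that its discretion does not apply.

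Third, there are safeguards: spirometry and a medication log at each induction (Section 7.3.4), a telephone call the next day to collect procedure-related events (Attachment 1), and separate serious-event reporting (Section 10.2.2). Section 11.1 also refers to a Study Reference Manual for safety monitoring, which is not available here, so the absence of a criterion is established for the protocol text only. These safeguards limit the exposure mainly to mild events that resolve by themselves. They do not settle whether such an event, once known, is entered.

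**Conclusion.** The contradiction is real and is in current text. Followed as written, Section 11.1 can lead to under-recording of mild related events after sputum induction and to adverse event listings that differ by site for reasons of practice alone. Site dependence is an inference from a multi-center study with an unspecified rule; the protocol does not demonstrate it. The size is unknown. Serious-event reporting and the biomarker objective are not touched.

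A reader might infer more, and the documents do not support it:

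- *That bronchospasm is the most frequent procedure-related event.* No frequency is given, and Section 11.1 applies its description of common effects to other symptoms.
- *That procedure-related events are the only safety outcome.* Section 9.5 also covers vital signs, and Section 10.2.2 covers deaths whether or not a procedure is involved, and hospitalizations with two exceptions.
- *That planned risk rates by cohort or procedure are biased by some stated amount.* The protocol plans no such rates, and any numerical range would only restate assumptions about event and recording probabilities.
- *That post-induction spirometry could stand in for the missing records.* Under Section 7.3.4 it follows a short-acting bronchodilator, so it is not a clean measure of change due to induction.

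**What to change.** Reconcile Section 11.1 with Section 10 by deleting the two discretionary sentences or aligning them with Section 10.2.1. The resulting text should say that any symptom after sputum induction that meets the Section 10.1.1 definition (new or worse than at baseline, and at least possibly related) is recorded with its severity grade. Investigator judgement should be confined to whether that definition is met. The list of expected effects can stay as a description of risk. If the Study Reference Manual contains recording guidance, it should be checked against the same rule.

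The cost is one paragraph of protocol wording and somewhat more CRF entry for mild events. No study procedure or clinical management changes.

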## **11.2 Regulatory Ethics Compliance**

### **11.2.1 Investigator Responsibilities**

The investigator is responsible for ensuring that the clinical study is performed in accordance with the protocol, current ICH guidelines on GCP, and applicable regulatory and country-specific requirements.

Good Clinical Practice is an international ethical and scientific quality standard for designing, conducting, recording, and reporting studies that involve the participation of human subjects. Compliance with this standard provides public assurance that the rights, safety, and well being of study subjects are protected, consistent with the principles that originated in the Declaration of Helsinki, and that the clinical study data are credible.

### **11.2.2 Independent Ethics Committee or Institutional Review Board (IEC/IRB)**

Before the start of the study, the investigator (or sponsor where required) will provide the IEC/IRB with current and complete copies of the following documents:

- Final protocol and, if applicable, amendments
- Sponsor-approved informed consent form (and any other written materials to be provided to the subjects)
- Sponsor-approved subject recruiting materials
- Information on compensation for study-related injuries or payment to subjects for participation in the study, if applicable
- Investigator's curriculum vitae or equivalent information (unless not required, as documented by IEC/IRB)

- Information regarding funding, name of the sponsor, institutional affiliations, other potential conflicts of interest, and incentives for subjects
- Any other documents that the IEC/IRB requests to fulfill its obligation

This study will be undertaken only after the IEC/IRB has given full approval of the final protocol, amendments (if any), the informed consent form, applicable recruiting materials, and subject compensation programs, and the sponsor has received a copy of this approval. This approval letter must be dated and must clearly identify the IEC/IRB and the documents being approved.

Approval for the genomic research component of the clinical study and for the genomic informed consent form must be obtained from the IEC/IRB. Approval for the protocol can be obtained independent of approval for genomic research.

During the study the investigator (or sponsor where required) will send the following documents and updates to the IEC/IRB for their review and approval, where appropriate:

- Protocol amendments
- Revision(s) to informed consent form and any other written materials to be provided to subjects
- If applicable, new or revised subject recruiting materials approved by the sponsor
- Revisions to compensation for study-related injuries or payment to subjects for participation in the study, if applicable
- Summaries of the status of the study at intervals stipulated in guidelines of the IEC/IRB (at least annually)
- Reports of adverse events that are serious, unlisted/unexpected, and associated with a study procedure
- New information that may adversely affect the safety of the subjects or the conduct of the study
- Deviations from or changes to the protocol to eliminate immediate hazards to the subjects
- Report of deaths of subjects under the investigator's care
- Notification if a new investigator is responsible for the study at the site
- Annual Safety Report and Line Listings, where applicable
- Any other requirements of the IEC/IRB

For all protocol amendments (excluding the ones that are purely administrative, with no consequences for subjects, data or trial conduct), the amendment and applicable informed

consent form revisions must be submitted promptly to the IEC/IRB for review and approval before implementation of the change(s).

At least once a year, the IEC/IRB will be asked to review and reapprove this clinical study. The reapproval should be documented in writing (excluding the ones that are purely administrative, with no consequences for subjects, data or trial conduct).

At the end of the study, the investigator (or sponsor where required) will notify the IEC/IRB about the study completion.

### **11.2.3 Informed Consent**

Each subject must give written consent according to local requirements after the nature of the study has been fully explained. The consent form must be signed before performance of any study-related activity. The consent form that is used must be approved by both the sponsor and by the reviewing IEC/IRB. The informed consent should be in accordance with principles that originated in the Declaration of Helsinki, current ICH and GCP guidelines, applicable regulatory requirements, and sponsor policy.

Before enrollment in the study, the investigator or an authorized member of the investigational staff must explain to potential subjects the aims, methods, reasonably anticipated benefits, and potential hazards of the study, and any discomfort participation in the study may entail. Subjects will be informed that their participation is voluntary and that they may withdraw consent to participate at any time. They will be informed that choosing not to participate will not affect the care the subject will receive for the treatment of his or her disease. Finally, they will be told that the investigator will maintain a subject identification register for the purposes of long-term follow-up if needed and that their records may be accessed by health authorities and authorized sponsor staff without violating the confidentiality of the subject, to the extent permitted by the applicable law(s) or regulations. By signing the informed consent form the subject is authorizing such access, and agrees to allow his or her study physician to recontact the subject for the purpose of obtaining consent for additional safety evaluations, if needed.

The subject will be given sufficient time to read the informed consent form and the opportunity to ask questions. After this explanation and before entry into the study, consent should be appropriately recorded by means of the subject's personally dated signature. After having obtained the consent, a copy of the informed consent form must be given to the subject.

Subjects will be asked to consent to participate in a genomic research component of the study (where local regulations permit). After informed consent for the clinical study is appropriately obtained, the subject will be asked to sign and personally date a separate genomic informed consent form indicating agreement to participate in optional genomic

research. A copy of the signed genomic informed consent form will be given to the subject. Refusal to participate will not result in ineligibility for the clinical study.

If the subject is unable to read or write, an impartial witness should be present for the entire informed consent process (which includes reading and explaining all written information) and should personally date and sign the informed consent form after the oral consent of the subject is obtained.

Subjects who are unable to comprehend the information provided can be enrolled only after obtaining consent of a legally-acceptable representative. Written assent should be obtained from subjects who are able to write. After having obtained the assent, a copy of the assent form must be given to the subject, and the subject's legally-acceptable representative.

When prior consent of the subject is not possible, enrollment procedures should be described in the protocol with documented approval/favorable opinion by the IEC/IRB to protect the rights, safety, and well being of the subject and to ensure compliance with applicable regulatory requirements. The subject or legally-acceptable representative must be informed about the study as soon as possible and give consent to continue.

